### Missing Data

For the primary outcome, an intention-to-treat analysis including all patients with at least baseline test data as a repeated observation of the dependent variable will be performed using a linear mixed model. Missing data will be assumed to be missing at random, and there will be no imputations [48]. A complementary per-protocol analysis will also be performed, with the inclusion criteria reported in detail. For the primary outcome analysis, participants will be included regardless of the availability of secondary outcomes, including MRI data.

### Ethical Considerations

This study has been conducted in accordance with the principles of the Declaration of Helsinki, and the protocol was approved by the Research Ethics Committee in the Capital Region of Denmark (reg. H-21047857; January 2022) and cannot be amended without reapplication. Furthermore, this study has been conducted in adherence to the study protocol and International Council for Harmonisation Good Clinical Practice guidelines, following applicable Danish and European law. The study does not fall under the scope of external monitoring, as it does not involve medical products or medical devices. Patients were covered by insurance through Rigshospitalet and the Danish Patient Compensation Association. Participation was voluntary, and inclusion required informed consent that could be withdrawn at any time by the participant.

### Protocol Amendments

The ethics protocol was extended for 1 year to accommodate the inclusion of 2-3 patients per week until December 2025.

## Results

The study was funded in December 2022. The ethically approved study protocol (H-21047857) was registered on ClinicalTrials.gov (NCT05785000), with study initiation on February 1, 2023. Enrollment and randomization of 70 patients were completed in March 2025. An overview of the study and patient recruitment and allocation is shown in Figure 1. The 12-week postintervention assessments concluded in August 2025, and data analysis is currently being performed, with finalization expected in 2026. The results will be reported in separate manuscripts in 2027.

Manuscripts reporting the study outcomes will be prepared for submission to peer-reviewed scientific journals, adhering to authorship guidelines. The following seven publications are planned (tentative titles):

A 12-week exercise intervention improves physical capacity in patients with prolonged post-concussion symptoms: an RCT study – the REPCon projectReduced cerebral oxygen metabolism in persistent post-concussion syndrome after mild traumatic brain injuryThe symptom complexity and intolerance in persistent post-concussion symptoms: insights from a controlled clinical studyPersistent post-concussion symptoms and clinical trial participation: a constructivist grounded theory studyBlood-brain barrier permeability is (not) increased in patients with prolonged post- concussion symptomsA 12-week exercise intervention does (not) improve reduced brain oxygen metabolism in patients with prolonged post-concussion syndrome: an RCT study – the REPCon projectUnderstanding the PPCS phenomenon through combined data using structural equation modeling and latent group statistics

Trial results will be presented at conferences and meetings and will be made accessible to the public through appropriate and relevant media, including negative, positive, or inconclusive results. In addition, findings will be communicated through presentations and dialogue with clinical practice stakeholders and patient organizations to ensure transparency, foster engagement, and support the translation of results into real-world settings.

**Figure 1. F1:**
[figure not shown]
Study flowchart providing an overview of the study and patient recruitment and allocation. CG: control group; MRI: magnetic resonance imaging; TG: treatment group.

## Discussion

We have presented the protocol for an RCT that evaluates the effect of an individualized physical aerobic graded exercise intervention in adults with PPCSs. The study has also used an intensive battery of physical and MRI-based examinations, as well as personal interviews and process evaluations. To our knowledge, this combined research methodology is scarce and could lead to a novel and integrated understanding of the complex phenomenon of persistent symptomatology and functional disabilities following PPCSs, where traumatology involves substantial neurological impairment. However, no single generally accepted pathophysiological component has been identified for this illness; rather, patients experience physical, neurological, cognitive, and perceptual inabilities. Combining an intervention study with an MRI-based investigation of brain physiology provides an opportunity to disclose the interaction between physical activity and brain function. While there is evidence for a beneficial effect of subsymptomatic exercise rehabilitation in patients with PPCSs [17,18], the impact on brain function is less known. Several MRI studies have pointed to microstructural abnormalities and possible changes in the brain functional connectivity network, using diffusion tensor MRI [49,50] and BOLD MRI [51,52]. Furthermore, autonomic dysfunction due to disturbances in brainstem function is of particular interest [11]. Clausen et al [53] and Mutch et al [54] have mentioned reduced carbon dioxide sensitivity and a lack of ability to increase ventilation during physical activity in patients with PPCSs. Reduced sensitivity to carbon dioxide results in abnormally high CBF during physical activity and may explain the exercise intolerance seen in many patients with PPCSs [53]. The findings by Clausen et al [53] underscore the importance of investigating brain physiology in this population. In this study, we have chosen a brain “stress” test consisting of a hypoxic challenge. This setup provides details regarding brain oxygen consumption, cerebrovascular reactivity, and the brain’s ability to increase glycolysis, which can manifest as an increase in brain lactate during hypoxia. The responses in young healthy individuals include maintained oxygen consumption, a pronounced increase in brain blood flow, and lactate production [30,33]. In older people, the ability to increase brain blood flow is diminished, and this results in a small but significant decrease in oxygen consumption [32]. Patients with sleep apnea show a reduced CBF response to hypoxia, and continuous positive airway pressure treatment has been found to normalize this pattern [29]. Patients with type 1 diabetes show a normal CBF response to hypoxia but significantly reduced lactate production during hypoxia, indicating impaired glycolytic activity [55]. In patients with multiple sclerosis (MS), the expected increase in blood flow is reduced, and a pronounced fall in oxygen consumption occurs ([name], unpublished data, May 2026). In this study on MS, vascular reactivity to carbon dioxide was tested and found to be normal. Hypercapnia and hypoxia induce cerebral vasodilation through different mechanisms [56]. In hypercapnia, carbon dioxide lowers local pH, which opens K^+^ channels in vascular smooth muscle cells, reduces Ca²^+^ influx, and thereby promotes vasodilation. Hypoxia induces vasodilation through a complex process that likely involves multiple mechanisms. Hypoxia stimulates nitric oxide release from nitric oxide synthase in both endothelium cells and neurons. Nitric oxide activates several enzymatic pathways, ultimately resulting in vasodilation and CBF increase. Thus, the hypoxic brain “stress” test investigates fundamental elements of brain physiology. The cerebrovascular response to hypoxia has not been systematically investigated in patients with PPCSs. The motivation to study BBB integrity is based on previous findings of increased BBB leakiness in both experimental mTBI animal models and patients with mTBI and PPCSs [15,57-60]. The BBB is important for maintaining proper brain function and a precise biochemical brain tissue environment while serving as a barrier against the entrance of toxic molecules, bacteria, and viruses. The function of the BBB is also highly related to vascular reactivity. In this study, we have used DCE MRI, which is a highly sensitive method that has been used previously for the detection of subtle leakiness in patients with MS [61-63].

This study is unique because it allows us to evaluate how an intervention consisting of subsymptomatic exercise can modify the anticipated disturbed brain physiology in patients with PPCSs. Moreover, the study aims to integrate novel neuropathophysiological insights with patient perspectives on the short- and long-term impacts of PPCSs on physical, neurobiological, and social functioning.

The study has some limitations. First, patients were not blinded to group allocation, and a desire to switch to the other group could have introduced unwanted bias, leading to lower compliance and poor protocol adherence. Second, patients were required to complete 4 MRI sessions (up to 6 hours) in a noisy environment, and for some patients with PPCSs, this might be challenging and provoke an increased symptom burden. Thus, it was decided to modify the approach and consider not completing all 4 MRI sessions as acceptable. Third, patients in the TG were required to meet in person twice weekly for the 12-week aerobic exercise protocol, and this could potentially affect the primary outcome. To support participation compliance, flexible scheduling was offered. Furthermore, practical factors, such as traffic delays, canceled trains, and seasonal illnesses, might have made it difficult for patients to attend the planned sessions. Finally, participants in the TG received a higher level of supervision and clinical contact compared to those in the CG, which might have introduced a risk of attention bias.

This study is innovative in its approach to patients with PPCSs, focusing on the effect of an individualized exercise regimen and exploring the neurofunctional underpinnings of symptom improvements and the patient perceptions of dealing with PPCSs. The findings are anticipated to contribute greatly to the field of PPCS management, potentially transforming current rehabilitation practices, alleviating symptom burden, and improving recovery from mTBI.

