### MRI Protocol

The participants completed 2 MRI sessions (scan sessions A and B) at baseline and after the intervention period. An overview of MRI data collection is shown in Table 2. The MRI scans were performed at the Department of Clinical Physiology and Nuclear Medicine, Rigshospitalet, using a Philips 3T dStream Achieva MRI scanner with a 32-channel phased-array head coil.

**Table 2. T2:** Overview of data collection and MRI^a^ measurements in the study.

Variable	Week 0	Week 4	Week 8	Week 12
Diffusion				
Mean diffusivity and anisotrophy	✓	—^b^	—	✓
Blood-brain barrier permeability	✓	—	—	✓
Cerebral blood flow	✓	—	—	✓
Capillary transit time heterogeneity	✓	—	—	✓
MR^c^ spectroscopy				
Brain lactate (normoxia)	✓	—	—	✓
Brain lactate (hypoxia)	✓	—	—	✓
MRI cerebral flow measurement by phase-velocity mapping and susceptometry				
Global mean cerebral blood flow (normoxia)	✓	—	—	✓
Global mean cerebral blood flow (hypoxia)	✓	—	—	✓
Global mean oxygen consumption (normoxia)	✓	—	—	✓
Global mean oxygen consumption (hypoxia)	✓	—	—	✓
MRI arterial spin labeling and visual stimulation				
Occipital cerebral blood flow (rest)	✓	—	—	✓
Occipital cerebral blood flow (visual stimulation)	✓	—	—	✓

a MRI: magnetic resonance imaging.

b Not applicable.

c MR: magnetic resonance.

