### Statistical Analysis

The primary outcome of this RCT study is an increase in time to symptom exacerbation during the BCBT from before to after the 12-week intervention. To evaluate this effect while avoiding sensitivity to false-positive error from repeated measurements on the same participant, we will use a linear mixed model. To assess the effect of the intervention, a regressor indicating either pre- or postintervention (Time) and a regressor indicating group allocation (Group) will be included as fixed effects. Participant identification will be included as a random effect (*u*) to account for repeated measurements. Sex and age may influence these results, and they will be included as fixed effects. The additional effect of group allocation and pre- and postintervention on the results of the BCBT will be included as an interaction term (Group_i_ and Time_ij_). This interaction term will provide the main result of the RCT study. The model is formulated as follows:

$$\begin{array}{c} Y_{ij}=\beta_{0}+\beta_{1}{\text{Group}}_{i}+\beta_{2}{\text{Time}}_{ij}+\beta_{3}({\text{Group}}_{i}\times {\text{Time}}_{ij})\\ +\beta_{4}{\text{Age}}_{i}+\beta_{5}{\text{Sex}}_{i}+u_{i} \end{array}$$

where *Y* is the duration (in minutes) of exercise on the bicycle until symptom provocation and *β*s are regression coefficients, with *β*_3_ representing the primary result of the RCT. The subscript *i* denotes the subject, and the subscript *j* denotes pre- or postintervention measurement.

For MRI parameters, 2 main tests will be performed for the baseline data. These analyses will be repeated after the 12-week intervention period and will include the intervention as a regressor, as explained in the following text. At baseline, the CMRO2 level (overall oxygen consumption of the brain) between healthy control participants and patients with PPCSs will be tested using ordinary least squares regression adjusted for age and sex, with heteroscedasticity-consistent SEs to account for possible nonconstant error variance. To investigate whether the physiological response to hypoxic exposure differs between patients with PPCSs and healthy controls, we will test whether the change in CMRO2 from hypoxic exposure differs between the groups. Initially, we will assess differences at baseline (preintervention) using a mixed linear regression as follows:

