Structural equation modeling (SEM) and latent class analysis (LCA) will be used to identify latent variables and subgroups associated with PPCSs. Both approaches will be applied in an exploratory framework to generate hypotheses for future research. In the SEM analyses, observed variables will be treated as manifestations of an underlying normally distributed latent construct representing PPCS severity. The model will include the summed Rivermead score, time cycled and maximal workload during the BCBT, MRI-based CMRO2 measurements under normoxia and hypoxia, and BBB permeability. The latent variable will be scaled to the summed Rivermead score to facilitate interpretation. By integrating information across multiple domains, we aim to obtain a more comprehensive and sensitive representation of symptom severity than can be obtained with any single measure alone. Conceptually or procedurally related indicators (eg, fatigue-related items, BCBT variables, and MRI measures) will be modeled to account for residual correlations by including terms describing local dependence. This is performed to avoid inflating latent factor loadings or identifying spurious subgroups driven by unmodeled shared variance. In the LCA analyses, observed variables will be treated as indicators of an underlying categorical latent variable. Patients will thus be grouped according to their multivariate response profiles. The number of classes will be estimated using information criteria (Akaike information criterion and Bayesian information criterion) and by excluding solutions with very small or clinically uninterpretable classes. Given the limited sample size, we will restrict models to a maximum of four classes. For each class, we will estimate the expected response pattern and assess whether the resulting classes have meaningful clinical interpretations. Associations between latent outcomes and external covariates, such as age and sex, will be examined post hoc, with covariates treated as external variables rather than incorporated directly into the latent variable models. This includes assessing whether patients are exercise-intolerant, defined by both clinical criteria and self-reported experience. Finally, we will extend the models to incorporate both baseline and follow-up data. In the SEM analyses, we will estimate the effect of the intervention on the latent PPCS construct, while in the LCA analyses, we will test whether the intervention effect differs across latent classes.

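### MRI sessions may be missed for symptom-related reasons, but the stated MRI models adjust only for age and sex, so selection bias of unknown size and sign cannot be excluded

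*Protocol article*

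**What the plan says.** **What was planned and what was relaxed.** The MRI Protocol section states: "The participants completed 2 MRI sessions (scan sessions A and B) at baseline and after the intervention period". Session A yields blood-brain barrier (BBB) permeability and diffusion. Session B yields CMRO2 and lactate under normoxia and hypoxia. In its limitations, the Discussion says of four noisy sessions that for some patients "this might be challenging and provoke an increased symptom burden", and then: "Thus, it was decided to modify the approach and consider not completing all 4 MRI sessions as acceptable".

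**Missing data.** The section opens with "For the primary outcome, an intention-to-treat analysis including all patients with at least baseline test data" and adds "Missing data will be assumed to be missing at random, and there will be no imputations". It mentions MRI once: "For the primary outcome analysis, participants will be included regardless of the availability of secondary outcomes, including MRI data".

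**MRI models (Statistical Analysis).** Baseline CMRO2 in patients and healthy controls "will be tested using ordinary least squares regression adjusted for age and sex, with heteroscedasticity-consistent SEs". BBB permeability gets a linear regression with the same two covariates. The baseline and 12-week hypoxia models are mixed models, again with age and sex and no symptom measure.

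**What is available.** Table 1 lists the RPQ and the bike test at weeks 0, 4, 8 and 12.

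**The concern.** The article itself gives symptom provocation as the reason for accepting incomplete MRI. An ordinary regression without imputation rests on those who were scanned. It estimates the intended contrast only if, given group, age and sex, being scanned is unrelated to the MRI value. The stated reason puts that in doubt, and the model leaves out the one symptom score that could make the assumption more plausible. The mixed models do use partial data, but missing at random is then conditional on what those models contain, which again excludes symptoms.

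At stake is the wording of the MRI papers. The planned titles in Results leave open a negative finding on BBB permeability and on exercise and oxygen metabolism. A null obtained in patients who tolerate scanning could be reported as a null for all patients with persistent symptoms.

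**Working it through.** The plan gives no figure for skipped sessions or for the severity–MRI relation, so there is nothing to reproduce. What follows is a scenario calculation.

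**Inputs from the article:** 70 randomized patients; 30% tentative dropout (Sample Size Calculation), borrowed as an upper end for skipping because no scan-specific figure exists; age and sex as the only covariates.

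**Assumed inputs:** 35 healthy controls; true patient-minus-healthy difference d = 0.5 SD; skipping 10–30%, logistic in standardised severity S with log-odds slope 1 or 2 per SD; within-patient correlation r between S and the MRI value (in the direction of abnormality) of 0.2–0.5.

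**Formula.** With patient value = d + r·S + noise, the expected scanned-only difference is d + r·m, where m is the mean of S among scanned patients.

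| Skipping | Slope | m | r = 0.2 | r = 0.3 | r = 0.5 |
|---|---|---|---|---|---|
| 10% | 1 | −0.09 | 0.48 | 0.47 | 0.45 |
| 10% | 2 | −0.14 | 0.47 | 0.46 | 0.43 |
| 30% | 1 | −0.25 | 0.45 | 0.42 | 0.37 |
| 30% | 2 | −0.37 | 0.43 | 0.39 | 0.31 |

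- Smallest loss: 0.2 × 0.09 ≈ 0.02 SD. Largest: 0.5 × 0.37 ≈ 0.19 SD.
- At 30% skipping, 70 × 0.7 = 49 patients are scanned. The standard error is √(1/49 + 1/35) ≈ 0.22, so the loss there (0.05–0.19 SD) is about 0.2–0.9 of a standard error.
- At r = 0 the estimate stays at 0.50.
- At r = −0.3 with 30% skipping and slope 2 it rises to 0.5 + 0.3 × 0.37 ≈ 0.61, so the sign reverses.

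**Does RPQ help?** The standardised estimate fits the regression on RPQ among scanned patients and evaluates it at the mean RPQ of all 70.

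- If RPQ itself drives skipping and is linearly related to the MRI value, simulation returns about 0.50. The standard error rises by at most about 5–6% (for example 0.220 to 0.233).
- If RPQ correlates only 0.6 with the true driver, about a quarter to a third of the bias is removed. At 30% skipping, slope 2 and r = 0.5, the estimate moves from 0.31 to about 0.37, not to 0.50.

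**Which contrast is touched.** Two of the four sessions are at baseline and two at follow-up. Skipped baseline sessions affect the patient-versus-healthy tests. Skipping only at follow-up leaves those tests intact and bears on the training-versus-control contrast, where bias can arise if the relation between severity and being scanned differs by arm, for example because training lowers symptoms.

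**The case against.** **Condensed article.** Missing-data handling for secondary outcomes may sit in a fuller plan that is not shown, and the missing-at-random sentence names no outcome, so it could be read as general. That is fair, and the absence of a detailed policy is not the point. The article does fix the MRI models and their covariates, and it states a symptom-related reason for missing scans. Even on the general reading, those covariates do not support the assumption.

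**Stronger readings.** A reader might infer that the patient-versus-healthy difference is measured in the less symptomatic patients and therefore pulled toward zero. The article does not support this as fact. It says scanning might be hard for some, and does not say who skipped or which sessions. The structural equation model, in which "observed variables will be treated as manifestations of an underlying normally distributed latent construct representing PPCS severity", is exploratory, and its loadings may prove close to zero. It makes attenuation the direction the authors' own thinking suggests, but does not establish it. A reader might also see a contradiction between the MRI Protocol and the Discussion. There is none, since the latter describes a modification.

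**Size.** The BBB sample size assumes 1.0 SD. The worst loss above would leave 0.81 SD, about 3.7 standard errors (0.81/0.22), so a false null would be unlikely. At 0.5 SD the expected ratio is only about 2.3 (0.5/0.22) without any bias, so low power would be the larger cause of a null. Both remarks stand.

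**Remedy.** Full recovery in simulation follows from letting RPQ drive the skipping. RPQ covers the previous 24 hours, and noise or scan-length intolerance may be something else. This also stands, so RPQ standardisation is offered as a sensitivity analysis.

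**Conclusion.** The concern holds in conditional form. Incomplete MRI is accepted for a symptom-related reason, and the stated MRI models omit the collected symptom score that could make missing at random more credible. Bias requires both that more symptomatic patients skip and that severity is related to the MRI measures. If both hold and severity goes with abnormality, the patient-versus-healthy difference shrinks by about 0.02–0.19 SD over 10–30% skipping and correlations of 0.2–0.5. If severity and MRI are unrelated there is no bias, and if the relation is reversed the bias is away from zero. The skipping rates, correlations, 0.5 SD difference and 35 controls are all assumptions. The primary bike-test analysis is not affected.

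**What to change.** 1. **Between-arm MRI models:** add baseline RPQ as a covariate. Where the target is an interaction, as in the hypoxia model, carry RPQ into that interaction too, because a main effect shifts only the level.
2. **Patient-versus-healthy regressions:** keep the age- and sex-adjusted models. Beside them, report as a sensitivity analysis an estimate standardised to the mean baseline RPQ of all randomized patients, by adding Patient × (RPQ − that mean), set to 0 for healthy controls. State that it reduces bias only to the extent that RPQ captures why patients skipped.
3. **Reporting:** give completion of sessions A and B by arm and time, with baseline RPQ of completers and non-completers. If the standardised and scanned-only estimates differ, limit any conclusion of no increase or no improvement to patients who tolerate scanning.

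**Cost:** a little extra programming and a standard error up to about 5–6% larger for the standardised estimate. No new data are needed, and the article says analysis is still under way.
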